### Best medical treatment

Patients randomized to the best medical treatment arm were not undergoing any catheterization procedure but were treated with antithrombotic medication. Since there is no consensus on the most effective medical therapy in preventing recurrent stroke or TIA in patients with PFO and paradoxical embolism, the choice of antithrombotic therapy, either antiplatelet therapy or oral anticoagulation, was left to the discretion of the treating physician. However, all patients randomized to the best medical treatment arm had to be treated with at least one antithrombotic medication. The recommended antithrombotic regimen in this study was oral anticoagulation for a period of 6 months (to be commenced at the time of inclusion in the study), followed by treatment with acetylsalicylic acid 100 mg to 325 mg per day during the remainder of the study. However, alternative treatment regimens using only oral anticoagulation or antiplatelet drugs or a combination of these medications were specifically allowed as considered necessary by the responsible physician. This is in keeping with the goal of the study to compare percutaneous PFO closure against best medical treatment, meaning medical treatment deemed optimal for the individual patient by the responsible physician. The recommended therapeutic range for patients who are orally anticoagulated in this study was an international normalized ratio (INR) of 2.0-3.0. A crossover from oral anticoagulation to antiplatelet therapy with acetylsalicylic acid, ticlopidine, or clopidogrel or vice versa was allowed within the best medical treatment arm. The date of drug therapy change and the reasons was documented in the case record form (CRF). Furthermore, events leading to interruption of antithrombotic therapy or bleeding complications were recorded as adverse events in the follow-up section of the CRF. Medical treatment was commenced immediately after randomization, unless already en route. Any events leading to interruption of antithrombotic therapy as well as any bleeding complications were recorded as adverse events.

The statistical power of this study was based on the population allocated to the best medical treatment group as a whole. Although differences among the different antithrombotic regimens will be analyzed, the statistical power may be inadequate to allow firm respective conclusions.

### Adverse events

#### Risk of percutaneous PFO closure

The risks of percutaneous PFO closure using the *Amplatzer PFO Occluder *consist of the risk of the implantation procedure and the long-term risk of the device itself. The implantation risks are similar to those of other interventional cardiac procedures [20]. They include complications related to vascular access (1-2%; e.g. bleeding, hematoma, need for transfusion), cardiac perforation with or without tamponade (<1%) [21-26], or air embolism (1-2%). The risks of stroke and myocardial infarction are expected to be lower than with coronary angiography which requires arterial access. The risk of death is minimal.

Complications intrinsic to the PFO device include device embolization (3-6%) primarily into the right circulation. Usually, the device can be retrieved either percutaneously, rarely surgery is needed. Other potential hazards include thrombus formation in the implantation equipment or on the device surface with the risk of subsequent embolization, infective endocarditis, or device collapse due to structural fatigue. Bleeding due to the post implantation medical management is another hazard.

#### Risk of medical treatment

The risks of medical treatment relate to adverse events of antithrombotic therapy. Bleeding is the main complication of oral anticoagulant therapy with warfarin or alike [27,28] and is influenced by the intensity of anticoagulation and the concomitant use of antiplatelet agents. The bleeding risk appears higher in patients with a history of prior stroke or gastrointestinal bleeding. Intracranial hemorrhage is estimated to occur with an incidence of 0.5% per year in patients on oral anticoagulant therapy with coumadin. Another important, but uncommon adverse effect of coumadin is skin necrosis. Furthermore many other medications and food components interfere with the metabolism of oral anticoagulants, potentiating or inhibiting their effects.

The principal adverse effects of acetylsalicylic acid are prolonged bleeding due to inhibition of platelet function, stomach irritation, gastritis, or gastrointestinal bleeding. These complications are rare and the therapeutic benefit of acetylsalicylic acid outweighs these potential adverse advents. Acetylsalicylic acid increases the risk for intracranial hemorrhage minimally. In case of intolerance to acetylsalicylic acid, ticlopidine or clopidogrel were used. Adverse event definitions for both treatment modalities are shown in Appendix 4.

### Statistical Methods

The working hypothesis of this study postulates a reduction in the annual incidence of recurrent thromboembolic events from 3% per year to ≤1% per year in patients with percutaneous closure of the PFO. With an overall sample size of 410, the power will be 80% at an α-level of 0.0492 (allowing for one interim analysis) under the following assumptions: mean follow-up time 4.5 years; successful closure of the PFO in 95% of those randomized to PFO closure; and annual rate of patients lost to follow-up 0.5%. The comparability between the two treatment groups will be tested with the two sample t-test or Fischer's exact test as appropriate, for continuous covariates, and Pearson's chi square test for categorical variables. An adjusted alpha level of 0.01 will be used as indication for an imbalance between the study groups.

The data from all participating centers will be pooled for the analysis of all primary and secondary endpoints as well as adverse events. An intention-to-treat analysis will be carried out retaining all the randomized study participants irrespective of whether they received the allocated treatment or not. Analysis of primary and secondary end points will be done using proportional hazard models. Graphical representation and comparison of survival between the two intervention groups will be presented using Kaplan Meier survival curves. Secondary analyses of these end points stratified by age, (age ≥45 years vs. <45 years and presence or absence of ASA) and effect modification by age and ASA will be tested in multivariable modeling. The significance level to reject the null hypothesis is set to 0.0492 (two-sided) taking account of the planned interim analysis.

An interim analysis will be conducted after 2.5 years of follow-up of the entire study population to detect an important excess in benefit or risk of closure of the PFO as compared to medical treatment. The significance level to define statistically a significant excess or reduction in risk will be 0.0054 (two-sided) according to O'Brian-Fleming boundaries. Data and Safety Monitoring Board is entitled to interrupt the trial taking into account both, clinical and statistical significance of excess or reduction in risk.

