### Study endpoints

The primary objective of this study is to investigate whether percutaneous PFO closure using the *Amplatzer PFO Occluder *is superior compared to best medical treatment in the prevention of symptomatic, recurrent thromboembolism. The following combined primary endpoint will therefore be assessed at each scheduled follow-up visit: death, nonfatal stroke, and peripheral embolism.

Patients who experience a primary endpoint event during the study period no longer have to continue the treatment allocated at the time of randomization. The management of patients who suffer a primary endpoint event will be left to the discretion of the responsible physician. Crossover from medical treatment to PFO device closure or vice versa from PFO device closure to additional antithrombotic treatment will be allowed in case of a primary endpoint event. However, all patients will continue to be followed up for further events after an initial primary endpoint according to the study protocol for the total duration of this study. Appendix 1 details the primary and secondary endpoints.

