### Secondary endpoints

a. New arrhythmia: any rhythm disorder other than normal sinus rhythm, requiring either hospitalization or pharmacologic or electrical therapy interventions.

b. Myocardial infarction: CK-MB >3 times the upper limit of normal and present in two separate blood samples or new pathological Q-waves in at least two contiguous leads with any elevated CK-MB.

c. Rehospitalization related to PFO or its treatment: >24 hour in-hospital stay, which becomes necessary for the management of complications related either to the PFO or antithrombotic therapy.

d. Device problems (dislodgment, structural failure, infection, thrombosis etc.)

e. Bleeding complications related to antithrombotic therapy will be classified as severe, if requiring any blood transfusion, and minor, if not requiring blood transfusions.

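### The proportional hazards rule for secondary endpoints should except device problems, because the between-arm hazard ratio for that endpoint is either not estimable or reflects only crossover

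*Protocol article*

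**What the plan says.** Four places in the protocol article bear on this.

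- **Model.** Statistical Methods: "Analysis of primary and secondary end points will be done using proportional hazard models". No endpoint is excepted. The same section adds analyses of these endpoints stratified by age and atrial septal aneurysm, with tests of effect modification by both.
- **Population.** Also Statistical Methods: the analysis is by intention-to-treat, "retaining all the randomized study participants irrespective of whether they received the allocated treatment or not".
- **Endpoint.** Appendix 1, Secondary endpoints, item d: "Device problems (dislodgment, structural failure, infection, thrombosis etc". The other four items are new arrhythmia, myocardial infarction, rehospitalization and bleeding.
- **Exposure.** Best medical treatment: "Patients randomized to the best medical treatment arm were not undergoing any catheterization procedure". Study endpoints: "Crossover from medical treatment to PFO device closure or vice versa" is permitted in case of a primary endpoint event, and follow-up continues for the full study.

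**The concern.** A proportional hazards model compares the rate of an event in two groups that are both at risk of it. Only one arm is assigned the device that can dislodge, fail, become infected or thrombose. The medical arm has no one at risk of endpoint d until a patient there has had a primary event and crossed over. Intention-to-treat then counts any device problem in that patient against medical treatment.

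At stake is how one of the risks of closure is reported. A clinician weighing closure wants to know how often an implanted device causes trouble. The hazard ratio prescribed for this endpoint does not answer that, and the planned stratified and effect-modification analyses inherit the same difficulty.

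**Working it through.** **Inputs.** From Statistical Methods: total sample size 410; event rates 3% and 1% per year; mean follow-up 4.5 years; successful closure in 95%; loss to follow-up 0.5% per year; two-sided alpha 0.0492; power 80%. From Adverse events: device embolization 3-6%. Assumed: 1:1 allocation, so 205 per arm; embolization standing in for all device problems; the share of medical-arm patients who cross over after a primary event.

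**1. The plan's own figure.** The closure-arm rate is 0.95 × 1% + 0.05 × 3% = 1.1% per year. The probability of an observed event, with event rate r, loss rate l and t = 4.5 years, is r/(r + l) × [1 − exp(−(r + l)t)].

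- Medical: 0.03/0.035 × [1 − exp(−0.1575)] = 0.1249
- Closure: 0.011/0.016 × [1 − exp(−0.072)] = 0.0478

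A two-proportion calculation with 205 per arm gives power 0.794 (0.799 ignoring losses). The stated 80% is reproduced and is not in dispute. The medical-arm figure gives 205 × 0.1249 = 25.6 expected primary events, which step 4 uses.

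**2. Expected closure-arm device events.** 205 × 3% ≈ 6 and 205 × 6% ≈ 12.

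**3. No medical-arm events.** With n1 closure and n0 medical patients at risk, each closure-arm event adds b − log(n1·e^b + n0) to the log partial likelihood, where b is the log hazard ratio. Its slope, n0/(n1·e^b + n0), is positive for every b, so the likelihood rises without reaching a maximum. For simulated data with 6 versus 0 events:

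| b | 0 | 2 | 5 | 10 | 20 |
|---|---|---|---|---|---|
| Log partial likelihood | −36.06 | −32.64 | −31.91 | −31.87 | −31.86 |

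The software fit does not converge; it stops at b of about 25 with a standard error of about 100,000. Some inference survives: the likelihood-ratio statistic is 8.4 and the lower 95% profile limit for the hazard ratio is about 2.7. For 12 versus 0 they are 17.0 and about 5.9.

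**4. Some medical-arm events through crossover.** If a share c of the 25.6 patients crosses over and a fraction q of those has a device event, the expected count is 25.6 × c × q and the chance of none is (1 − q)^(25.6c).

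| q | c | Expected medical-arm device events | Chance of none |
|---|---|---|---|
| 3% | 25% | 0.19 | 82% |
| 3% | 100% | 0.77 | 46% |
| 6% | 25% | 0.38 | 67% |
| 6% | 100% | 1.54 | 21% |

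One event makes the ratio finite. For 12 versus 1, the log hazard ratio is 2.51 with standard error 1.04, so the ratio is exp(2.51) ≈ 12, with limits exp(2.51 ± 1.96 × 1.04) of about 1.6 to 95.

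What that ratio measures can be seen from the expected counts: (205 × q)/(25.6 × c × q) = 8.0/c. The device event rate q cancels. The ratio of counts is about 8 if everyone crosses over, 16 if half do and 32 if a quarter do, whatever the device's actual safety.

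**5. The alternative.** The one-arm incidence can be estimated directly. As an illustration with denominator 205, 6/205 = 2.9% (exact 95% CI 1.1-6.3%) and 12/205 = 5.9% (3.1-10.0%).

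**The case against.** The strongest reply is that this is a one-line summary in a journal article. It suits four of the five secondary endpoints, and a full protocol or analysis plan, not shown here, may treat device problems descriptively. Any analyst would see that the comparison is uninformative. That limits the weight of the point but does not remove it: the article states a rule whose wording covers endpoint d, and the point is about that rule, not about omitted detail.

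A reader might go further and infer that the hazard ratio cannot exist. The documents do not support this. Crossover is permitted and can make the ratio finite. Even with no medical-arm events, a likelihood-ratio test and a lower limit are available. They do not help much, since they test whether device problems are as frequent in the arm not assigned a device.

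A reader might also infer that device safety would go unestimated. That too is unsupported. Statistical Methods plans Kaplan-Meier curves by group and a pooled analysis of adverse events. Implantation complications are recorded as adverse events (Implantation procedure), Table 1 has a row for procedural complications, and Appendix 4 defines device embolization and complications requiring device removal. A closure-arm incidence could be drawn from these. What stands is that the curves are specified by randomized group, and no stated analysis targets risk among implanted patients.

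Finally, the 95% closure assumption might be read as 5% of the closure arm having no implant and diluting the denominator. The article treats completeness of closure as a six-month echocardiographic finding and expects residual shunt immediately after implantation, so unsuccessful closure does not mean no device.

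**Conclusion.** The point holds as a minor fault, wrong as written, confined to one of five secondary endpoints. Followed literally, the rule gives a hazard ratio for device problems that either has no finite estimate (a 21% to 82% chance of no medical-arm event in the scenarios shown) or is set by the extent of crossover. Neither is a meaningful treatment comparison. That reasoning rests only on the stated model, population, endpoint and crossover rule. The event counts and probabilities also depend on 1:1 allocation, on the 3-6% embolization figure representing all device problems, and on assumed crossover shares of 25-100%. The primary analysis and the alpha level are untouched.

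**What to change.** Add one sentence to Statistical Methods that excepts endpoint d from the proportional hazards comparison, and from the stratified and effect-modification analyses that follow it. Report device problems among all patients who received a device, as a proportion with an exact 95% confidence interval and as cumulative incidence with time counted from implantation. List implants in medical-arm patients who crossed over separately. Keep proportional hazards models under intention-to-treat for arrhythmia, myocardial infarction, rehospitalization and bleeding, all of which can occur in both arms.

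The cost is that sentence and one table. Device problems are already an endpoint at each visit, and patients who cross over stay in follow-up, so no new data are needed. If a fuller document already handles endpoint d this way, the article's sentence only needs to be brought into line with it.

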### Patient selection criteria

Patients with PFO and presumed paradoxical embolism who meet all inclusion criteria but no exclusion criteria of Appendices 2 and 3 are offered to participate in this study. After obtaining a written informed consent, patients were randomised in 29 centers of Europe, Canada, and Australia. Randomization started February 2000. Enrolment of 414 patients was completed in February 2009. All patients will be followed-up longitudinally as outlined in Table 1. Follow-up is maintained until the last enrolled patient is beyond 2.5 years of follow-up (expected in 2011).

**Table 1 T1:** Timetable of prospective investigations during the study.

	Baseline	Hospitalization	6 months	1 year	2 years	3 years	4 years	5 years
History	x		x	x	x	x	x	x
Listing of antithrombotic medications	x	x	x	x	x	x	x	x
Laboratory survey	x							
12 lead ECG	x	x	x	x	x	x	x	x
Holter ECG	x							
TEE*	x	X (TTE or TEE)	x					(x)
CT/MR or angiography of region of interest (brain or periphery)	x							
Carotid Doppler	x							
Employment status	x		x	x	x	x	x	x
Quality of life	x		x	x	x	x	x	x
Stroke outcome classification (NIH SS, Barthel index, Modified Rankin scale)	x	x	x	x	x	x	x	x
Procedural complications		x						
Primary endpoints			x	x	x	x	x	x
Secondary endpoints			x	x	x	x	x	x

*TEE examination after 6 months and possibly yearly thereafter until complete closure of the PFO has been documented. A TEE at 5 years of follow-up or termination of the study is optimal; a TTE is acceptable immediately following device closure.

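### The stated levels of 0.0054 (interim) and 0.0492 (final) have O'Brien-Fleming shape at half information, but the constant is slightly too liberal for the implied overall 5%

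*Protocol article*

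**What the plan says.** All the figures are in the Statistical Methods section of the protocol article.

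- Interim level: the threshold "will be 0.0054 (two-sided) according to O'Brian-Fleming boundaries".
- Final level: "The significance level to reject the null hypothesis is set to 0.0492 (two-sided) taking account of the planned interim analysis".
- Power: "the power will be 80% at an α-level of 0.0492 (allowing for one interim analysis", with N = 410.
- Timing: "An interim analysis will be conducted after 2.5 years of follow-up of the entire study population". The sample-size assumptions give "mean follow-up time 4.5 years".

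The section on patient selection adds: "Follow-up is maintained until the last enrolled patient is beyond 2.5 years of follow-up (expected in 2011". The article states no overall alpha. A final level just under 0.05, described as allowing for the interim look, implies a two-sided 5%.

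**The concern.** When a protocol names a boundary family and gives both nominal levels, the pair can be checked. The final level leaves 0.05 − 0.0492 = 0.0008 for the interim look. That is little for a look at 0.0054, unless the two test statistics are so highly correlated that nearly every interim crossing would also be a final rejection.

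The level 0.0492 is the criterion for rejecting the primary null hypothesis, and it is also the alpha in the power statement. If it is too lenient for the look that is actually taken, a final p-value just below it would be called significant without 5% control. With an interim at 0.0054 and half information, the affected range is roughly 0.048 to 0.0492.

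**Working it through.** **Inputs.** From Statistical Methods: interim two-sided level 0.0054, so z1 = 2.782; final two-sided level 0.0492, so z2 = 1.967; one interim look; 2.5 years and a mean of 4.5 years of follow-up; event rates "from 3% per year to ≤1% per year in patients with percutaneous closure of the PFO"; 95% successful closure; 0.5% per year lost; N = 410. Assumptions: an overall two-sided alpha of 0.05 and 205 patients per arm.

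**Step 1: the plan's power.** With rate h, loss rate d = 0.005 and T = 4.5 years, the expected event proportion is h/(h + d) × [1 − exp(−(h + d)T)].

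- Medical arm, h = 0.03: 0.1249.
- Closure arm, h = 0.95 × 0.01 + 0.05 × 0.03 = 0.011: 0.0478.

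A two-proportion test with 205 per arm at 0.0492 has 79.4% power (79.9% without losses). The stated 80% therefore reproduces to rounding.

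**Step 2: shape of the pair.** Classical O'Brien-Fleming has z1 = c/√t and z2 = c, so t = (z2/z1)². Here (1.967/2.782)² = 0.50. The shape is right at half information, with c = 1.967.

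**Step 3: overall error.** Error = 1 − P(|Z1| < 2.782 and |Z2| < 1.967), where Z1 and Z2 are bivariate normal with correlation √t.

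| Information fraction t | Overall two-sided error |
|---|---|
| 0.40 | 5.20% |
| 0.50 | 5.13% |
| 0.556 (2.5/4.5) | 5.09% |
| 0.60 | 5.06% |
| 0.70 | 5.00% |
| 0.80 | 4.95% |
| 0.90 | 4.92% |

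The error crosses 5% at t = 0.7025. A simulation of 20 million pairs agrees (5.13% at t = 0.50, 5.00% at t = 0.70). At t = 0.50 the look adds 5.13 − 4.92 = 0.21 points to the final level, while only 5.00 − 4.92 = 0.08 points were set aside. The shortfall is 0.13 points.

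**Step 4: levels that hold 5%.**

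- Classical O'Brien-Fleming at t = 0.50: c = 1.977, levels 0.0052 and 0.0480.
- Interim kept at 0.0054: final level 0.0479 at t = 0.50, about 0.0482 to 0.0483 at t = 0.556, and 0.0492 only at about t = 0.70.
- Final kept at 0.0492: interim level about 0.0026 at t = 0.50 or 0.0031 at t = 0.556.

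**Step 5: can one timing give both stated levels at 5%?** None was found among the variants tried.

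- Classical: an interim of 0.0054 needs t = 0.506, with final 0.0479; a final of 0.0492 needs t = 0.403, with interim 0.0019.
- Lan-DeMets O'Brien-Fleming-type spending: an interim of 0.0054 goes with a final of 0.0478 (t = 0.496, two-sided 0.05 form) or 0.0483 (t = 0.558, twice the one-sided 0.025 form).

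**Step 6: where the look falls.** Read as mean follow-up, t is 2.5/4.5 = 0.556. Counted in expected events under the Step 1 rates it is 0.57, and the error is 5.08%. Read as 2.5 years for every patient, the look coincides with the end of follow-up. Then t is near 1 and the error is close to the final level itself, about 4.9%.

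**Step 7: power after correction.** Step 1 repeated at 0.0480 gives 79.1%.

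**The case against.** A reader might infer that the levels are not an O'Brien-Fleming pair at all. Step 2 shows otherwise: the shape is exact at half information, and only the constant is off, by about 0.01.

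A reader might also infer that the final threshold is too lenient whatever happens. The documents do not support that either. The timing sentence, taken literally beside the end-of-follow-up rule, puts the look at the end of the trial, where the pair is mildly conservative. The 5.09% needs the mean-follow-up reading, which the text does not state. This objection stands, and it makes the size of the error conditional on timing. It does not rescue the pair: at that timing 0.0054 is no longer an O'Brien-Fleming level, and the look is hardly an interim one.

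Three further points on the other side are fair. The 5% target is inferred. The monitoring board may, but need not, act on a crossing, so 5.13% is an upper bound: a crossing that neither stops the trial nor persists to the final analysis produces no rejection. And the excess is about a tenth of a percentage point. These bear on how serious the point is, not on the arithmetic.

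**Conclusion.** The point holds in limited form. At the only information fraction where the two levels fit the named boundary, they do not hold the implied 5%: the overall error is at most 5.13%, an excess of 0.13 points. On the mean-follow-up reading the excess is 0.09 points. From about 70% information onwards there is no excess, but the levels are then not O'Brien-Fleming. So no reading of the timing gives both the named boundary and 5% control at the stated levels.

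This rests on an overall two-sided alpha of 0.05, on the usual joint normal approximation for the two statistics, and on counting every interim crossing as a rejection. Severity is minor. The arithmetic is firm; which error figure applies depends on a timing that the article leaves open to two readings.

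**What to change.** State the overall two-sided alpha. Define the interim look by an information fraction or an event count, in terms that cannot coincide with the end of follow-up. Name an O'Brien-Fleming-type spending function, including whether it spends 0.05 two-sided or 0.025 on each side, and compute both levels from it at the observed fraction.

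The pair 0.0052 and 0.0480 is right for classical O'Brien-Fleming at exactly half information and should not be fixed without that timing. If a look has already been taken at 0.0054, keep that level and set the final one from the observed fraction: 0.0479 at t = 0.50, or about 0.0482 to 0.0483 at t = 0.556. If no look precedes the final analysis, use 0.05. Carry the resulting level into the power statement.

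The cost is a sentence or two and two numbers. Power moves by about 0.3 points (79.4% to 79.1% at 0.0480); sample size and conduct do not change.
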